### Sample size calculation

Millbourn et al. found a decrease in the incidence of incisional hernia from 18% to 5,6% in a randomized controlled trial [34]. In this trial, follow-up consisted of clinical instead of radiological examination for incisional hernia occurrence. In this trial, ultrasound examination will be used in order to be able to diagnose incisional hernia with higher sensitivity. It is expected that a relative decrease of the incidence incisional hernia after one year of 50% is reasonable. The mean reported one year incidence of incisional hernia in literature is 15%[1-5]. In order to reduce the mean incidence of incisional hernia from 15 to 7.5%, power calculations showed that two groups of 259 evaluable patients each are needed (power = 0.80, alfa = 0.05). Loss to follow-up is estimated at 10% of included patients. A total of 576 patients (2 × 288) will be included in the study to correct for loss to follow-up. Overall effects will be calculated adjusted for predictive baseline characteristics, which will lead to a higher statistical power.

### Statistical analysis

Descriptive statistics will include median and interquartile range for continuous variables, and absolute numbers (with %) for categorical variables. Randomized groups will be compared for imbalance without formal statistical testing. Analysis will be by intention-to-treat. Differences between randomized groups will be tested with appropriate statistical methods, including t-tests or Mann-Whitney tests for continuous variables (considering whether the normality assumption is rejected by the Kolmogorov-Smirnov test with Lilliefors correction test), and chi-square tests for categorical variables. The primary outcome (incisional hernia) will be analyzed with Kaplan-Meier analysis and a Cox regression analysis, to adjust for any loss to follow up between 30 days and 1 year after surgery. The primary analysis is a covariate adjusted Cox model, which includes the following predefined, well-establihed predictors of incisional hernia: abdominal aneurysm aorta (AAA), obesity, diabetes, corticosteroid usage, radiotherapy, COPD, smoking, age, cancer, inguinal hernia, cardiovascular disease and collagen disorders.

Subgroup effects will be assessed by tests of interaction to prevent overinterpretation of apparent differences in effectiveness. Quality of life data will be analyzed by paired T-tests, comparing baseline with follow-up measurements, and repeated measures analysis. A two-sided p < 0.05 will be taken to indicate statistical significance.

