### Operation data

• Type of operation

• Suture length: wound length ratio

• Number of stitches

• Length of incision

• Closure time

• Blood loss

• Operation time

• Antibiotic prophylaxis

• Drains and location

• Thrombosis prophylaxis

• Pain medication

• Peroperative complications (intestinal lesions, bleeding, other)

• Epidural catheter

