#### Postoperative data

• Blood transfusion

• Postoperative ventilation and duration

• Postoperative corticosteroids

• Postoperative radiation therapy

• Postoperative pain medication

• Postoperative ileus and duration

• Postoperative complications:

○ Centers for Disease Control criteria for Surgical Site Infection, according to the guidelines proposed by Mangram in 1999 [36] Appendix 1.

○ Wound haematoma: accumulation of blood in the wound area, which warrants surgical exploration and intervention.

○ Pulmonary infections

○ Ventilation problems

○ Re-admission and indication

○ VAS pain score until day 6 post operative

At 1 and 12 months, ultrasound imaging will be performed to examine the midline for any asymptomatic clinically not detectable incisional hernias. Size and location of any incisional hernias will be registered.

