### Outpatient clinic follow up

• Outpatient clinic visit at 1 and 12 months

○ Incisional hernia

○ Wound infection

○ Seroma formation

○ Other wound problems

○ Other abdominal wall hernia

• Ultrasound at 1 and 12 months

• VAS pain scores and Quality of Life forms preoperatively (day of operation or the day before) and at 1,3, 6 and 12 months

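### VAS pain falls under unadjusted two-group tests, which are valid but give up precision that the preoperative VAS, and an epidural in place at randomisation, could supply

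*Protocol article*

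**What the plan says.** Pain is listed under Secondary outcome, and the Objective section narrows it to wound pain during the first month. Postoperative data lists "VAS pain score until day 6 post operative". Outpatient clinic follow up adds "VAS pain scores and Quality of Life forms preoperatively (day of operation or the day before) and at 1,3, 6 and 12 months". A baseline pain score therefore exists, on the same schedule as quality of life. Operation data lists "Epidural catheter" without a time of placement. Pain medication is recorded both there and under Postoperative data.

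For continuous variables, Statistical analysis says "Differences between randomized groups will be tested with appropriate statistical methods, including t-tests or Mann-Whitney tests for continuous variables", with the choice between the two resting on a normality test. The one covariate list in that section belongs to the primary Cox model and holds risk factors for hernia, with neither preoperative VAS nor epidural. Comparison with baseline and repeated-measures analysis are named for quality of life, not for pain.

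Two other statements bear on the point. Randomisation procedure starts allocation 15 minutes before closure and balances it by centre and by surgeon or resident. Sample size calculation says that effects will be adjusted for prognostic baseline factors and that this raises power.

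**The concern.** The article accepts that adjusting for prognostic baseline factors buys power, but carries this through only for hernia. VAS pain has a baseline value and repeated scores. It is still left to a two-group test, which uses neither and, applied occasion by occasion, gives a set of separate p-values and no single estimated arm difference.

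Preoperative VAS precedes allocation. An epidural placed for the operation would normally precede it too, since allocation comes only shortly before closure. If these variables predict early pain, leaving them out widens the confidence interval for the arm difference. At stake is how well the trial can detect, or rule out, a difference in wound pain. The hernia result is not affected.

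**Working it through.** **The plan's own figure.** No figure is stated for pain. The only sample size is for hernia: "In order to reduce the mean incidence of incisional hernia from 15 to 7.5" per cent, giving "two groups of 259 evaluable patients each are needed (power = 0.80, alfa = 0.05"), with "A two-sided p < 0.05 will be taken to indicate statistical significance" and "Loss to follow-up is estimated at 10% of included patients". It reproduces with Schoenfeld's formula:

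- HR = ln(0.925)/ln(0.85) = 0.480
- events = 4 × (1.960 + 0.842)² / (ln 0.480)² = 58.2
- per arm = 58.2 / 0.1125 / 2 = 258.6, so 259
- with 10% loss: 259/0.90 = 287.8, so 288 per arm and 576 in total

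It serves here only to supply the 259 evaluable patients per arm used below.

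**Cost of not adjusting.** Let R² be the share of VAS variance explained by preoperative VAS and epidural together. The documents give no value, so R² is assumed. The calculation treats VAS as compared by means.

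- Standard error without adjustment relative to with: 1/√(1 − R²)
- Equivalent sample size: 259/(1 − R²) per arm
- Detectable difference at 80% power: (1.960 + 0.842) × √(2/259) × √(1 − R²) = 0.246 × √(1 − R²), in SD units

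| R² (assumed) | SE larger without adjustment | Equivalent n per arm | More patients | Detectable difference (SD) | Power for 0.2 SD |
|---|---|---|---|---|---|
| 0 | – | 259 | – | 0.246 | 62% |
| 0.05 | 2.6% | 273 | 5% | 0.240 | 65% |
| 0.10 | 5.4% | 288 | 11% | 0.234 | 67% |
| 0.20 | 12% | 324 | 25% | 0.220 | 72% |
| 0.30 | 20% | 370 | 43% | 0.206 | 78% |

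**Is 0.05 to 0.30 a sensible range?** For the epidural alone, with share q and effect D in within-group SDs, R² = q(1 − q)D² / (1 + q(1 − q)D²).

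- q = 0.3, D = 0.3: 0.0189/1.0189 = 0.019
- q = 0.5, D = 1.0: 0.25/1.25 = 0.20

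So the epidural's own contribution runs from negligible to moderate. Preoperative VAS adds r² of what remains (taking the two as unrelated). For example, assume half the patients have an epidural, it shifts VAS by 1.0 to 1.5 cm, the SD is 2.5 to 2.0 cm, and r is 0.2 to 0.4:

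- low end: 0.25 × 1.0²/2.5² = 0.04; combined 0.04 + 0.04 × 0.96 = 0.078; 1/(1 − 0.078) = 1.09
- high end: 0.25 × 1.5²/2.0² = 0.141; combined 0.141 + 0.16 × 0.859 = 0.278; 1/(1 − 0.278) = 1.39

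This example fixes epidural use at 50%, the share that maximises q(1 − q), so it favours adjustment.

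**Is the unadjusted test valid?** A simulation of 10,000 trials had 259 per arm, 50% epidural with an effect of 0.8 residual SD, a coefficient of 0.4 for a standardised preoperative VAS, and no arm effect. The plain t-test rejected in 5.0% of trials.

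**Chance imbalance in epidural use.** At 50% use, the between-arm difference in epidural share has SD √(0.25 × 2/259) = 0.044. Times 1.0 to 1.5 cm, this moves the estimate by 0.04 to 0.07 cm. The standard error of the difference is 2.0 to 2.5 cm × √(2/259) = 0.18 to 0.22 cm, which already includes that variation.

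**The case against.** The strongest reply is that this is a condensed article and that the model for one secondary outcome commonly sits in an analysis plan that is not shown. The wording also introduces its tests with an inclusive term, so other methods are not excluded, and the sample size section speaks of adjustment in general terms. This stands in part: the text does not forbid adjustment. But the point rests on a method that is named, not on silence. The general promise of adjustment appears in the hernia calculation and names no pain covariate, and quality of life receives a repeated-measures analysis on the same schedule while pain does not. Unadjusted tests remain the natural reading.

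A reader might infer three stronger things, and the documents support none of them.

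- *That uneven background analgesia biases the pain comparison.* Allocation is random, type I error holds, and chance imbalance is ordinary sampling error already inside the standard error. Minimisation by centre also balances whatever part of epidural use differs between centres.
- *That epidural and preoperative pain are strong determinants here.* The article gives no SD, share, effect or correlation for VAS.
- *That the epidural is certainly a baseline variable.* Placement before allocation is plausible, but its time is not stated. Epidural dosing or duration after closure, and postoperative pain medication, follow allocation and are not baseline covariates.

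Equal VAS scores could also hide unequal analgesic use. The article already records postoperative pain medication, however, and its general methods allow it to be compared by arm, so this adds little as a criticism.

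**Conclusion.** The point holds as a modest, optional gain in efficiency for one secondary outcome. The named analysis is valid and unbiased but leaves out a baseline score the trial already collects and an epidural record that is usable if it reflects status at randomisation. For an assumed R² of 0.05 to 0.30, the unadjusted standard error is about 3% to 20% larger, equivalent to about 5% to 43% more patients, and power for a 0.2 SD difference would rise from 62% to between 65% and 78% with adjustment. The true figure could lie at or below the lower end. The range is meant for early VAS. An epidural effect need not persist to month 1, so the same gain should not be claimed there.

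**What to change.** In Statistical analysis, take VAS pain out of the general two-group test and prespecify one repeated-measures linear model for the scores to day 6 and month 1, with:

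- arm, day and arm by day;
- preoperative VAS;
- epidural present at randomisation (yes/no) with an epidural-by-day term, because a constant effect from the first days through month 1 would be misspecified;
- the minimisation factors, centre and surgeon or resident.

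Report the arm difference with its confidence interval. Present postoperative analgesic use by arm as an outcome, and do not enter it as a covariate.

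The cost is mainly analysis wording, since VAS, epidural and pain medication are already collected. The data form should make clear that the epidural item means in place at randomisation. The downside is slightly more modelling and a stated rule for missing preoperative VAS, which may arise in the emergency laparotomies that the trial admits.

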### Participants

Patients scheduled for an elective abdominal operation through a midline incision will be asked for informed consent at the outpatient clinic or in hospital on the day preceding the day of surgery. Also, emergency laparotomies can be included in this trial if the patient is able to sign the informed consent. We intend to investigate the efficacy of the small bites technique in all risk groups. This also includes oncological gynaecological patients in centers with at least 50 median laparotomies a year.

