#### Outcome parameters

##### Primary outcome

• Primary outcome will be incisional hernia occurrence within one year after surgery, either clinically and/or ultrasonographically detected.

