#### Monitoring

The Erasmus University Medical center is the sponsor of this trial. Adverse events are defined as any undesirable experience occurring to a subject during a clinical trial, whether or not considered related to the investigational intervention. All adverse events reported spontaneously by the subject or observed by the investigator or his staff will be recorded. A serious adverse event (SAE) is any untoward medical occurrence or effect that at any dose results in death; is life threatening (at the time of the event); requires hospitalization or prolongation of existing inpatients' hospitalization; results in persistent or significant disability or incapacity; is a new event of the trial likely to affect the safety of the subjects, such as an unexpected outcome of an adverse reaction, major safety finding from a newly completed animal study, etc. All SAEs will be reported to the accredited Medical Ethical Committee (MEC) that approved the protocol, according to the requirements of that MEC. Serious Adverse events are death and burst abdomen. Adverse Events are readmission and reoperations.

An independent data and safety monitoring committee will evaluate the progress of the trial and will examine safety parameters every 3 months. The committee can unblind the data whenever deemed necessary based on reported adverse events. All involved physicians will repetitively be asked to report any potential adverse events caused by the study protocol. These adverse events will be listed and discussed with the monitoring committee. The monitoring committee can ask for a full report in order to discuss a specific adverse event. A copy of this report will be sent to the central ethics board and to the involved physicians. All deceased patients will be evaluated by the safety committee for cause of death and possible trial related serious adverse effects. Every death will be reported to the central ethics board and the local ethics board. The Data Safety Monitoring Board will consist of an epidemiologist/statistician and two independent surgeons.

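### Kaplan-Meier is planned for the one-year hernia outcome with no separate handling of death; if deaths are censored, each arm's incidence and the absolute difference are somewhat overstated, while the primary Cox comparison stands

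*Protocol article*

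**What the plan says.** All references are to the protocol article.

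- **Endpoint (Primary outcome).** "Primary outcome will be incisional hernia occurrence within one year after surgery, either clinically and/or ultrasonographically detected". Death is not a component.
- **Method (Statistical analysis).** The outcome is analysed by "Kaplan-Meier analysis and a Cox regression analysis, to adjust for any loss to follow up between 30 days and 1 year after surgery". The next sentence adds: "The primary analysis is a covariate adjusted Cox model". Loss is the only reason given for incomplete follow-up. The section does not say how a death before hernia is coded.
- **Population (Participants; Statistical analysis).** Gynaecological cancer patients are eligible. "Also, emergency laparotomies can be included in this trial if the patient is able to sign the informed consent". The Cox covariates include aortic aneurysm, cancer, cardiovascular disease and age.
- **Deaths (Monitoring).** Death is listed as a serious adverse event, and every death goes to the ethics boards. "All deceased patients will be evaluated by the safety committee for cause of death". No mortality figure is given.
- **Use of the absolute effect (Economic evaluation).** The main economic outcome is the cost per hernia avoided within a year: the difference in mean costs divided by the difference in mean effects. For subgroups with similar costs, the absolute benefit is said to determine cost-effectiveness.

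**The concern.** Kaplan-Meier censoring assumes that a censored patient could still have the event later. That can be reasonable for a patient who moves away. It is not reasonable for a patient who has died, because death rules the hernia out. With deaths censored, 1-KM estimates the risk in a population in which nobody dies, which is higher than the proportion of operated patients who have a hernia by one year.

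The consequence falls on absolute quantities: the incidence in each arm, the risk difference and the cost per hernia avoided. Mean costs would naturally cover everyone operated on, including those who die. An effect taken from 1-KM would refer to a different, death-free population, so the two parts of the ratio would not match. Aneurysm, cancer, age and cardiovascular disease enter the prognostic index for subgroup cost-effectiveness and plausibly also predict death, so the mismatch could be largest in those subgroups.

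**Working it through.** **1. The plan's own figures.** Sample size calculation: "In order to reduce the mean incidence of incisional hernia from 15 to 7.5"%, "two groups of 259 evaluable patients each are needed (power = 0.80, alfa = 0.05"). The Schoenfeld log-rank formula reproduces this:

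- Hazard ratio = ln(0.925)/ln(0.85) = 0.480.
- Events = 4 × (1.960 + 0.842)² / (ln 0.480)² = 58.2.
- Patients = 58.2 / 0.1125 = 517.2, where 0.1125 is the mean of 0.15 and 0.075. That is 258.6, rounded up to 259 per arm.
- With 10% loss: 259/0.9 = 287.8, rounded up to 288 per arm, 576 in all.

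The rates 15% and 7.5% are used below as the values that 1-KM would show.

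**2. Assumptions.** One-year mortality m is not in the documents; 5, 10 and 15% are used as a range. Mortality is taken as equal in both arms and independent of hernia, and deaths are taken as censored.

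**3. Case A: hernia and death at constant rates over the year.** With a = −ln(1−p) and b = −ln(1−m), the cumulative incidence is a/(a+b) × [1 − (1−p)(1−m)].

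Example, p = 0.15 and m = 0.10: a = 0.1625, b = 0.1054, so 0.1625/0.2679 × (1 − 0.85 × 0.90) = 0.6067 × 0.235 = 0.1426.

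**4. Case B: every hernia is found at the 12-month visit.** Patients who died have left the risk set by then, so 1-KM gives the risk among those still alive. The share of all operated patients is p × (1−m).

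Example: 0.15 × 0.90 = 0.135.

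**5. Results (large bites / small bites).**

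| Assumed mortality | 1-KM shows | Case A | Risk difference A (points) | Case B | Risk difference B (points) |
|---|---|---|---|---|---|
| 5% | 15.0 / 7.5% | 14.6 / 7.3% | 7.3 | 14.3 / 7.1% | 7.1 |
| 10% | 15.0 / 7.5% | 14.3 / 7.1% | 7.1 | 13.5 / 6.8% | 6.8 |
| 15% | 15.0 / 7.5% | 13.9 / 6.9% | 6.9 | 12.8 / 6.4% | 6.4 |

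Risk differences are computed before rounding: 7.32, 7.13 and 6.95 in case A; 7.125, 6.75 and 6.375 in case B. The 1-KM risk difference is 7.5 points throughout.

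**6. Cost per hernia avoided.** For a fixed cost difference, moving from the 1-KM risk difference to the one in the table multiplies the size of the ratio by 7.5/7.32, 7.5/7.13 and 7.5/6.95 (about 1.02, 1.05 and 1.08) in case A. In case B the factor is 1/(1−m): 1.05, 1.11 and 1.18.

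**7. Relative effect.** The ratio of the two cumulative incidences is 0.50 in both cases (0.499 at 15% mortality in case A), as in the plan.

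**The case against.** **The omission may be settled elsewhere.** The article does not state that deaths are censored, that 1-KM will be the reported incidence, or that it will feed the economic analysis. A condensed protocol may leave these to the full protocol or analysis plan. This stands in part: the overstatement is conditional. But the article does fix the method and its purpose, and under that method a hernia-free death is ordinarily censored. Naming a better estimator is therefore a comment on what is written.

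**The primary result might seem invalid.** A reader might infer that the plan rests on Kaplan-Meier alone and that the treatment comparison is biased. The text does not support this. Cox regression is named in the same sentence, and the adjusted Cox model is primary. Censoring deaths there gives a cause-specific hazard ratio, a legitimate comparison under the usual assumptions.

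**The larger figures might be taken as the estimate.** Case B is an upper bound. Patients are also examined clinically and by ultrasound at 1 month, and a clinical diagnosis at any time within the year counts. No figure says what share of hernias is found at 12 months. Both cases should be shown.

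**The trial might seem too small.** Because 288 × 0.90 = 259.2, the allowance has no slack, and a reader might conclude that deaths leave too few evaluable patients. That is not shown. "Loss to follow-up is estimated at 10% of included patients", and this may already include deaths, since the target is stated in evaluable patients. If 10% deaths did come on top of 10% other loss, case A would still give 58.6 expected hernias against the 58.2 required. Case B would give 2 × 288 × 0.9 × 0.9 × 0.1125 = 52.5. A shortfall thus depends on mortality and detection timing, neither of which the documents give. The plan also expects covariate adjustment to add power. Whether the 10% covers deaths is at most a point to clarify.

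**Conclusion.** The point holds for absolute incidence only. If hernia-free deaths are censored, as the named method ordinarily does, 1-KM overstates control-arm incidence by 0.4, 0.7 and 1.1 points in case A at an assumed mortality of 5, 10 and 15%. In case B the overstatement is 0.75, 1.5 and 2.25 points. The risk difference is overstated by about 0.2 to 0.6 points in case A and 0.4 to 1.1 points in case B.

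The direction is certain once deaths are censored. The size rests on a mortality rate and a detection pattern that the documents do not give, and on equal mortality by arm. The primary cause-specific Cox test is unaffected. The change is worth making because the economic outcome uses the absolute effect and the better estimate needs little or nothing that is not already recorded.

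**What to change.** In the Statistical analysis section or the analysis plan:

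- Define death before hernia as a competing event, separate from loss to follow-up.
- Report 12-month hernia incidence by arm with the Aalen-Johansen cumulative incidence function in place of 1-KM.
- Use the resulting risk difference for the cost per hernia avoided, including the subgroup estimates.
- Keep the covariate-adjusted Cox model as the primary test, describe its hazard ratio as cause-specific, and report deaths by arm beside it.
- As a clarification, add one sentence saying whether the 10% loss allowance includes deaths.

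The cost is wording and a standard estimator. Every death is already reported and reviewed. The downside is a slightly lower reported incidence and absolute benefit. The wording should be settled before outcome data are seen by arm.

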**Methods/Design:**

The STITCH trial is a double-blinded multicenter randomized controlled trial designed to compare a standardized large bite technique with a standardized small bites technique. The main objective is to compare both suture techniques for incidence of incisional hernia after one year. Secondary outcomes will include postoperative complications, direct costs, indirect costs and quality of life.

A total of 576 patients will be randomized between a standardized small bites or large bites technique. At least 10 departments of general surgery and two departments of oncological gynaecology will participate in this trial. Both techniques have a standardized amount of stitches per cm wound length and suture length wound length ratio's are calculated in each patient. Follow up will be at 1 month for wound infection and 1 year for incisional hernia. Ultrasound examinations will be performed at both time points to measure the distance between the rectus muscles (at 3 points) and to objectify presence or absence of incisional hernia. Patients, investigators and radiologists will be blinded during follow up, although the surgeon can not be blinded during the surgical procedure.

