### Randomisation procedure

The randomization process is started only 15 minutes before closure to prevent consequences due to the trial during the operation with the online TOP randomisation.

Patients will be randomized between closure with the large tissue bites technique or with the small tissue bites technique. Randomisation is stratified by center, and between surgeon or resident with a minimization procedure, ensuring balance within each stratum and overall balance. The randomization result will be given immediately by TOP. A confirmation email without randomization result will be send to the investigator.

Patients will be kept unaware of the type of closure until the endpoint of the trial. Surgeons or residents blinded for the procedure will perform out patient clinic controls. Postoperative ultrasonography will be performed by radiologists blinded for type of closure. The randomisation procedure, blinding and objectification of incisional hernia by ultrasound will provide the best possible data to support preference for the large bites technique or the small bites technique over the other for closure of the abdominal wall.

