##### Preoperative data

• Date of birth

• Length and weight

• Current smoker (Yes or No)

• Medical history (including chronic obstructive pulmonary disease (COPD), diabetes mellitus, cardiac disease, prior laparotomies)

• Preoperative radiotherapy or chemotherapy

• Preoperative or perioperative corticosteroids

• Previous abdominal operations

• Other abdominal wall hernias

• American Society of Anaesthesiologists (ASA) classification

• Width of linea alba (if preoperative Computed Tomography Imaging is available)

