Data on effects (reduction of incisional hernia), costs (time costs of new suture technique and material and development costs) and savings (reduced health care use of patients without incisional hernia) will all be collected in this study. Data on treatment (hospitalisation) and follow-up consultations will be collected retrospectively from (electronic) patient charts and hospital administration. This data will be collected by health care professionals using a data-collection form. Information will collected on:

- length of hospital stay

- length of stay in ICU

- reinterventions

Data on extramural care, work absence and other patient costs will be gathered via questionnaires at each follow-up (1 and 12 months).

For a description of the calculation of the effect measures see paragraph 'outcome parameters'.

Discounting of future costs and effects is not relevant because of the limited time horizon of 1 year. When costs of a treatment are similar across subgroups, the absolute benefit determines the cost-effectiveness of a treatment for a specific subgroup.

Randomized controlled trials are designed to evaluate the effects of treatment at the group level, and cost-effectiveness is usually calculated for this group as a whole. There could however be substantial and relevant between subgroup variability. It is therefore common to consider subgroup specific effects of interventions. The subgroup specific cost-effectiveness will be estimated by first deriving a prognostic index, based on the predefined predictors of incisional hernia: abdominal aneurysm aorta (AAA), obesity, diabetes, COPD, corticosteroid usage, radiotherapy, cardiovascular disease, smoking, age, cancer, other abdominal wall hernias and collagen disorders.

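### The primary Cox model leaves out centre and operator type, the two minimisation factors: a mildly conservative test and a small avoidable loss of power

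*Protocol article*

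**What the plan says.** Randomisation procedure section: "Randomisation is stratified by center, and between surgeon or resident with a minimization procedure, ensuring balance within each stratum and overall balance". The allocation factors are therefore centre and operator type.

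Statistical analysis section: "The primary analysis is a covariate adjusted Cox model, which includes the following predefined, well-establihed predictors of incisional hernia". The predictors named are "abdominal aneurysm aorta (AAA), obesity, diabetes, corticosteroid usage, radiotherapy, COPD, smoking, age, cancer, inguinal hernia, cardiovascular disease and collagen disorders". That is 12 items, all describing the patient. The article mentions no stratified Cox model, centre frailty or re-randomisation test, and gives no reason for leaving out the allocation factors.

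The Sample size calculation section justifies covariate adjustment by the gain in statistical power. The Abstract gives the number of sites: "At least 10 departments of general surgery and two departments of oncological gynaecology will participate in this trial".

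The predictor list also appears in the Economic evaluation section, with one entry worded differently. There the list ends "smoking, age, cancer, other abdominal wall hernias and collagen disorders", whereas in the Statistical analysis section it ends "smoking, age, cancer, inguinal hernia, cardiovascular disease and collagen disorders". The Preoperative data list records "Other abdominal wall hernias".

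**The concern.** Minimisation forces the arms to be alike on centre and operator type, so chance imbalance in those factors contributes almost nothing to the spread of the treatment estimate. A model that ignores them still computes its standard error as if that imbalance could occur. When the factors are prognostic, the reported standard error is larger than the true standard deviation of the estimate, so p-values are too large and power is lost.

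Both factors could plausibly be prognostic here. The sites mix general surgery with gynaecological oncology. The Discussion calls standardisation of technique difficult because of the many surgeons and residents taking part. The planned size has no reserve of power to absorb a loss.

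**Working it through.** **1. The plan's own sample size.**

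Inputs from the Sample size calculation section: one-year incidence 15% versus 7.5%, power 0.80, alpha 0.05, 259 evaluable per arm, 10% loss, 576 in total. The Statistical analysis section sets two-sided testing.

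- Hazard ratio: ln(0.925)/ln(0.85) = 0.480; its log is -0.735.
- Schoenfeld events: 4 × (1.960 + 0.842)² / 0.735² = 58.2.
- Per arm: 58.2 / (0.15 + 0.075) = 258.6, so 259.
- Loss: 259/0.9 = 287.8, so 288 per arm and 576 in total.
- Expected events: 259 × 0.225 = 58.3, giving power 0.801.

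The stated figures reproduce under the Cox/log-rank formula, and power sits at the target.

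**2. Effect of omitting the two factors.**

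The article gives no centre or operator heterogeneity, so these settings are assumed: 518 patients, 12 unequal centres (10 + 2), half the closures by residents, minimisation on the two factors with probability 0.8, exponential times censored at one year, and 2,500 runs per scenario. The control rate averages 15%. Null runs use that rate in both arms, about 518 × 0.15 = 78 events. The 12 predictors were not simulated.

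Null results with the factors omitted. The implied type I error is 2 × [1 − Φ(1.96 × SE/SD)].

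| Centre SD of log hazard; operator HR | Model SE | Empirical SD | SE/SD | Implied type I error |
|---|---|---|---|---|
| 0; 1 | 0.230 | 0.229 | 1.004 | 4.9% |
| 0.3; 1.25 | 0.230 | 0.228 | 1.009 | 4.8% |
| 0.5; 1.5 | 0.232 | 0.226 | 1.027 | 4.4% |
| 0.8; 2 | 0.236 | 0.223 | 1.058 | 3.8% |

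Rejection rates, factors omitted versus included (operator type plus centre indicators):

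| Scenario | Type I error | Power at HR 0.48 | Power difference |
|---|---|---|---|
| 0; 1 | 4.0% v 4.4% | 76.6% v 77.2% | 0.6 |
| 0.3; 1.25 | 4.2% v 4.6% | 76.5% v 77.3% | 0.8 |
| 0.5; 1.5 | 3.6% v 4.4% | 75.6% v 77.5% | 1.9 |
| 0.8; 2 | 3.6% v 4.7% | 72.2% v 76.0% | 3.8 |

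With the factors included, null SE and SD agree: 0.232 v 0.234 in the third scenario and 0.237 v 0.238 in the fourth.

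Monte Carlo error is about 0.4 points for type I error and 0.9 for power, although the compared analyses share the same simulated data. An SD from 2,500 runs has relative error of about 1/√5000 = 1.4%. The 2.7% excess in the third scenario is therefore only about twice its simulation error; the 5.8% excess in the fourth is clear.

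**3. Where the power goes.**

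The standard errors at HR 0.48 hardly differ between the two models: 0.285 v 0.286 in the third scenario and 0.288 v 0.289 in the fourth. What changes is the mean log hazard ratio: -0.733 v -0.754 and -0.714 v -0.753. Adding the factors therefore makes the interval match the estimator's variation; it does not make it visibly shorter.

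**4. Form of adjustment.**

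If each of the 12 predictors takes one parameter, treatment plus predictors plus operator type makes 14, or 58/14 = 4.1 events per parameter. Eleven centre indicators bring it to 25, or 58/25 = 2.3. Fixed centre effects are therefore unattractive.

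A separate simulation of a centre-stratified Cox model with operator as covariate used 12 centres, 518 patients, 11.25% events, centre SD 0.5 to 0.8 and operator log HR 0.4 to 0.6. Power rose from 76.5% to 77.7% at moderate heterogeneity and from 72.4% to 75.2% at larger heterogeneity.

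Stratifying a log-rank test by every centre-by-operator cell gains less. In the four scenarios above its power was 76.3%, 76.2%, 75.9% and 74.4%.

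**The case against.** A reader might infer that ignoring the minimisation factors makes the primary test invalid. It does not: every simulated type I error is below 5%, so the error is on the safe side.

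A reader might also infer that the hazard ratio is biased towards 1. In the strongest scenario the mean log hazard ratio without the factors is -0.714, a hazard ratio of 0.49 against the 0.48 used to generate the data. This is the usual difference between a conditional and a more marginal hazard ratio, not a bias of the trial.

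The stronger objections concern size, and they largely stand:

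- All heterogeneity values are assumed. What matters is the heterogeneity left after age, cancer, aneurysm, radiotherapy and the rest, and those predictors may carry much of the case-mix difference between departments.
- Even with no centre or operator effect, the model without the factors rejected in 4.0% of null runs, so a simulated 3.6% is not a fall from 5%. The SE/SD ratio is the steadier guide.
- Likewise, 0.6 points of the power difference are present with no effect at all. The net figure is 1.9 − 0.6 = 1.3 points in the moderate scenario and 3.8 − 0.6 = 3.2 in the strong one.

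It can also be said that the article is condensed, that the predictor list is not expressly exclusive, and that an analysis plan may add design factors. This stands only in part. The article names its primary model and enumerates the predictors as predefined, so a plan that followed it literally would omit both factors.

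The differing hernia entries are a separate matter and add nothing to the argument about allocation factors. A reader might conclude that inguinal hernia is the wrong entry or is not recorded. The article does not show which label was intended, nor that hernia type goes unrecorded.

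**Conclusion.** The point holds as a modest inefficiency. The stated primary model ignores both factors that govern allocation, without explanation and against the protocol's own aim of gaining power through adjustment.

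If the factors are prognostic beyond the listed predictors, the standard error is about 3% to 6% too large under the null in the moderate and strong scenarios, and the true type I error is about 4.4% to 3.8%. The power lost is negligible for weak factors, about 1 to 2 points for moderate ones, and up to about 4 points for strong ones. These sizes rest on assumed heterogeneity, centre sizes, share of residents and minimisation probability, and on a simulation without the 12 predictors; they may be too high. The direction is secure and the size is not.

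The required sample size is unaffected. The mismatch between the two hernia entries is a real inconsistency, because the two definitions could produce different primary models.

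**What to change.** In the primary Cox model, stratify the baseline hazard by centre, or use a centre frailty. Add operator type (surgeon or resident) as one covariate and keep the predefined predictors. Do not use fixed centre indicators with about 58 expected events. Do not stratify by every centre-by-operator cell, which gives back part of the gain.

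The cost is a sentence in the analysis plan. Both variables are already held in the randomisation system, and the number of patients does not change. The downside is that strata are thin, averaging 58/12 = 4.8 events per centre, so very small centres contribute little when stratified. A frailty term lessens this at the price of a distributional assumption.

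Separately, decide before analysis whether the predictor is inguinal hernia or other abdominal wall hernias. Use the chosen definition in the Statistical analysis and Economic evaluation sections, and check that the baseline form records it.
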